### Recruitment

We will utilise existing successful NSPCC Family SMILES referral pathways such as identifying families with the assistance of practitioners working in CYP services, CAMHS, Adult Mental Health services and education services. We will broaden the diversity of referral sources by working closely with NHS practitioners and services. We will apply for adoption by the National Institute for Health Research’s Clinical Research Network to support recruitment and the identification of suitable families via GP registers, Community Mental Health and Inpatient Teams, and rehabilitation units. Posters and flyers will be placed in appropriate NHS third sector organisations and schools, and practitioners working in the community will be informed of the study to assist with the generation of direct opportunistic referrals.

Recruiting gatekeepers will provide potential families with a study information pack including an invitation letter, information sheet and consent-to-contact form. Separate packs containing the same information will be provided to CYP and parents. If a family are interested in participating, they can return the consent-to-contact form, detailing their preferred method(s) of contact, directly back to the research team in the freepost envelope also included in the information pack. Families who are informed of the study by a practitioner or support worker will also have the opportunity to ask them to complete a contact form on their behalf and return it securely to the research team. Following receipt of a consent-to-contact form, the research team will contact the family, identify if the family are suitable based on the inclusion/exclusion criteria outlined previously and confirm that they are still interested in taking part. If eligible families will be informed that they will be contacted at a later stage to arrange and complete a face-to-face baseline interview at a convenient time and place. The timing of the baseline interviews will be dependent on the research team receiving enough referrals of the same age band at one site. Families will be contacted by telephone fortnightly during the waiting period by the research team to be informed of progress and to provide them the opportunity to answer any additional questions. A one-off home visit to discuss the study will also be offered.

At the face-to-face interview, the family will be given the opportunity to ask any further questions and written consent will be taken. As the CYP will be 16 years old or younger, they will be asked to give assent and consent from their parents/carer will be obtained in support of their child’s participation. Separate consent will be obtained for parents/carers who are also participating. It will be made clear to all family members that they can withdraw from the study at any point, without detriment to their care. If a parent wishes to withdraw, their child/children can still participate with their consent. If the parent has more than one child, all children in the family will be eligible to participate, but are not required to do so. If siblings are in the same age band, they will attend different groups.

After obtaining consent, family members wishing to participate in the study will be asked to complete the baseline measure booklet. All measures are standardised and have been designed as self-complete; however, the researcher will be able to offer any assistance when and if required. Outcome measure booklets will be age-dependent according to the age-range for which the measures have been designed. Families will receive a total of £50 shopping vouchers over the data collection time points for their participation in the study.

During the baseline and subsequent follow-up visits, trial researchers will identify if any adverse events have occurred and report as per agreed procedures. An identified member of the Trial Steering Committee (TSC) will monitor participant safety within the trial and will be responsible for reviewing any serious adverse events occurring as part of the trial.

### Randomisation

Following agreement to participate via written consent and completion of baseline outcome measures, families will be randomised on a 1:1 ratio either to Young SMILES or to usual care using a central, independent, free web-based system [34].

### Blinding

Randomisation will be conducted by the study co-ordinator to maintain blinding of the statistician and research team to reduce detection bias. To facilitate blinding, we will (1) ensure that families know that they can contact the study coordinator should they have any queries about their allocation or the Young SMILES intervention arrangements and (2) the researcher conducting the data collection visits will remind families to refrain from revealing their allocation to them during follow-up visits. Should a researcher become aware of any allocations, this will be recorded and reported.

### Analysis

#### Statistical analysis

##### Determine uptake, adherence and follow-up rates

The main focus will be on tabulated and associated graphical summaries of the key indicators of success of the study, including recruitment and participant flow. We shall report data in line with the Consolidated Standards of Reporting Trials (CONSORT) statement [35]. We shall also report the numbers of participants who drop out from the intervention, withdraw their consent and do not provide follow-up outcome data.

##### Intervention effectiveness

In order to inform a future definitive trial, we shall use standard linear regression to examine change in our HRQoL measures, Pediatric Quality of Life Inventory and KIDSCREEN, adjusting for baseline scores and the sex of the child. The presentation of the analysis will focus on point estimates and associated 95% confidence intervals. After obtaining point estimates of intervention effect and measure of variability of the outcomes, we will be able to design a definitive trial. As this is a feasibility trial, the subgroup analyses will not be conducted but will be addressed should a subsequent large scale trial be conducted.

If multiple children and parents are recruited from the same family, for the main analysis, we will identify an index child and parent for inclusion in the analysis from whom data will be collected. Other sibling(s) will still be offered the opportunity to attend Young SMILES (if their family is randomised to the intervention group). We shall ask parents to nominate the index child. We will discuss with parents which child should be ‘nominated’ as the index child. Parents will not be party to any data collected from their child/children. Since outcome data is collected for all children and parents, in a secondary analysis, we shall include all available data and use robust standard errors to account for clustering within families. Within-cluster variation due to the group intervention will be estimated for the main clinical outcomes in order to inform plausible intra-cluster correlations for sample size calculation of the main cluster RCT.

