#### Intervention – Young SMILES

Young SMILES is a service for CYP (aged 6–16) whose parents live with SMI, aiming specifically to improve the HRQoL of CYP. The intervention was co-developed in the earlier phase of this research via consultation with stakeholders (CYP of parents with serious mental illness, parents and practitioners from third sectors and NHS organisations). Young SMILES is an 8-week group programme (4–6 CYP per group) split into two age bands, namely 6–11 and 12–16. At week 4, five parallel sessions are offered to the parent or significant other adult. CYP and parent sessions last for 2 hours, which includes time for a short break and refreshments during and after the group. Where possible, the sessions will be held in a non-stigmatising venue such as a community location rather than a hospital clinic or school.

Sessions will be facilitated by two trained practitioners. The expertise and skills of the facilitators is an invaluable aspect of the Young SMILES intervention. Groups will be delivered in an NHS organisation using a co-delivery model where one facilitator is from the NHS (family therapy background) and the other is from a third sector organisation. Third sector organisation facilitators will have a variety of professional backgrounds such as social workers, children’s service practitioners, psychologists and occupational therapists.

Intervention facilitators will be provided with a 3-day training session. A training manual for facilitators was developed as part of the development phase which provides an overview of the feasibility trial and development of Young SMILES. It additionally incorporates structured detail on service delivery and intervention delivery, providing an on-going guide/reference for practitioners who deliver the service and manual to support trainers to ‘teach’ practitioners the aspects of the model and how it should be delivered.

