### Protocol changes

Since the trial commenced, a number of protocol changes have been made. These are detailed in Table 4. Applications to the Research Ethics Committee (REC)/HRA have been made and approved for all changes outlined.

**Table 4 Tab4:** Protocol changes made since the trial commenced

Aspect of trial	Changes made
Primary outcome point	Change from 3-months to 4-months. Due to family availability and referral rates, baseline interviews have been conducted over a longer time period than was anticipated. As a result, some families were being offered a 3-month follow-up appointment while still accessing the Young SMILES intervention (if randomised to that trial arm). To ensure the amount of ‘useful data’ is maximised, the primary outcome point was changed to 4 months, without altering the 6- and 12-month time points
Data collection	Addition of demographic questionnaire for all participants taking part in the feasibility trial (children and young people, parents, carers) Addition of referrer interviews to explore the experiences of individuals who have referred to the study and also those who have been approached but have not referred any families; individuals will be from health, social care, educational and third sector services, which will aid a more thorough understanding of the development of referral pathways that will add to the other findings from the feasibility study to assist with the development of an application for a full-scale trial
Randomisation	Change from using the Sealed Envelope system (www.sealedenvelope.com) to randomise 60 families on a 1:1 ratio either to Young SMILES or to usual care to online randomisation software (www.randomization.com), which would better meet study requirements in relation to sample size and the ability to stratify by age and site, without incurring costs Addition of 2:1 randomisation allocation procedures (2 Young SMILES intervention; 1 control) to expedite start of intervention groups; this has been acknowledged to be wholly appropriate for a feasibility trial in such a ‘specified group’ intervention
Intervention delivery	Inclusion of siblings within the same group (if in the same age band) Submission of young person travel consent form for parents/carers to consent to child/adolescent travelling to the intervention venue alone

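### The effectiveness analysis makes no allowance for Young SMILES group, so its 95% confidence intervals are too narrow if outcomes are correlated within groups

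*Protocol article*

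**What the plan says.** All of this is in the protocol article.

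- **Main model (Intervention effectiveness).** "we shall use standard linear regression to examine change in our HRQoL measures", "adjusting for baseline scores and the sex of the child". No term for intervention group is listed.
- **Unit of analysis (same section).** Where several family members take part, "for the main analysis, we will identify an index child and parent for inclusion in the analysis".
- **Output (same section).** "The presentation of the analysis will focus on point estimates and associated 95% confidence intervals".
- **Secondary analysis (same section).** For all children and parents, "we shall include all available data and use robust standard errors to account for clustering within families".
- **Group variation (same section).** "Within-cluster variation due to the group intervention will be estimated for the main clinical outcomes". The stated purpose is to supply ICCs for sizing the later trial, which the article calls a cluster RCT.
- **Delivery (Intervention – Young SMILES).** "Young SMILES is an 8-week group programme (4–6 CYP per group) split into two age bands, namely 6–11 and 12–16". Two facilitators run each session.
- **Siblings.** All eligible children in a family are offered the sessions (Sample size). Table 4 under Protocol changes adds: "Inclusion of siblings within the same group (if in the same age band".

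**The concern.** Families are randomised individually, but in one arm only the children are then treated together. Children in a group share facilitators, peers and eight weeks of sessions. The article also lets facilitators adapt activities to the group in front of them (CYP group sessions; Parent/carer group sessions). Outcomes within a Young SMILES group may therefore be correlated, while control families have no such structure. This is a partially nested design.

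Ordinary linear regression assumes independent errors. Restricting the main analysis to one index child per family removes correlation between siblings, but index children from different families still share groups. Robust standard errors clustered on family have the same gap, because two families in one group count as independent. The plan thus expects a group correlation, since it will estimate one, yet reports intervals that set it to zero.

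Two things are at stake. One is the width of the intervals for the HRQoL effects. The other is the group ICC handed on to the definitive trial: siblings may now share a group, so an ICC taken from all children without a family effect would count sibling similarity as group similarity.

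**Working it through.** **Inputs.** Sixty families, 30 per arm (Sample size). A 2:1 allocation was added later (Table 4) with no date given, so 40:20 is used as the other extreme. Groups hold 4–6 children; five is taken as the middle. The article gives no ICC, so 0.05, 0.10 and 0.20 are assumed. There is no power calculation to reproduce: the size follows a pilot-study recommendation, 2 × 30 = 60.

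**Index children per group, m.** The 4–6 counts all children, but the main model uses one per family. If every attending family brings one child, m = 5. If families bring 1.5 attending children on average (an assumption), m = 5 / 1.5 ≈ 3.3.

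**Formula.** Take equal total variance in the two arms and group correlation in the intervention arm only. The design effect there is DE = 1 + (m − 1) × ICC, and

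true SE / reported SE = √{[DE/n_I + 1/n_C] / [1/n_I + 1/n_C]}

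At 30:30 this reduces to √[(DE + 1)/2], and at 40:20 to √[(DE + 2)/3].

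| m | ICC | DE | Ratio at 30:30 | Ratio at 40:20 |
|---|---|---|---|---|
| 5 | 0.05 | 1.20 | √1.100 = 1.049 | √1.067 = 1.033 |
| 5 | 0.10 | 1.40 | √1.200 = 1.095 | √1.133 = 1.065 |
| 5 | 0.20 | 1.80 | √1.400 = 1.183 | √1.267 = 1.125 |
| 3.3 | 0.05 | 1.117 | √1.058 = 1.029 | √1.039 = 1.019 |
| 3.3 | 0.10 | 1.233 | √1.117 = 1.057 | √1.078 = 1.038 |
| 3.3 | 0.20 | 1.467 | √1.233 = 1.111 | √1.156 = 1.075 |

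**Refinement.** Clustering also lowers the pooled residual variance slightly. Its expectation, relative to the true variance, is [(n_I − DE) + (n_C − 1)] / (n_I + n_C − 2). For m = 5, ICC 0.10 and 30:30 this is (28.6 + 29)/58 = 0.993, and the ratio becomes 1.095/√0.993 = 1.099. The refined ratios for m = 5 are 1.051, 1.099 and 1.191 at 30:30, and 1.035, 1.068 and 1.133 at 40:20.

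**Range over group size.** With 4 to 6 index children per group, the refined ratios at 30:30 are 1.04–1.06, 1.08–1.12 and 1.15–1.24 for the three ICCs. At 40:20 they are 1.03–1.04, 1.05–1.09 and 1.10–1.17.

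**Coverage of the nominal 95% interval.** This was simulated with 20,000 trials per setting, m = 5, and regression on arm, baseline (assumed correlation 0.5) and sex.

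| ICC | 30:30 | 40:20 |
|---|---|---|
| 0 | 95.0% | 94.9% |
| 0.05 | 94.1% | 94.2% |
| 0.10 | 92.9% | 93.5% |
| 0.20 | 90.4% | 91.4% |

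A second simulation, of 6,000 trials per setting with a pooled-variance t interval, gave 94.4%, 93.1% and 90.9% at 30:30, and 94.6%, 93.2% and 91.7% at 40:20.

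**The case against.** The case against giving this much weight is substantial.

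- **It is not the trial's headline result.** A reader might infer that the principal output is wrong. The documents do not support that. The Statistical analysis section puts the main focus on recruitment, participant flow and follow-up, and none of the listed objectives is an effect estimate. Clustering leaves those rates untouched. This stands.
- **The interval drives no stated decision.** The section plans no hypothesis test and ties no progression rule to the interval. What goes forward is the point estimate, which this omission does not bias, the outcome variability and the ICC. This stands and limits the consequence, although the intervals remain the stated focus of the effectiveness reporting.
- **The narrowing is conditional and modest.** It is tempting to say flatly that the intervals are too narrow. With no ICC in the documents, that holds only if the ICC is above zero; at zero there is no error. Using five per group also overstates the effect whenever siblings attend. Both points stand.
- **The sibling problem depends on an unstated choice.** The article does not say which data will yield the group ICC. If index children are used, siblings do not arise. It would be wrong to say that the planned ICC is contaminated; it could be.
- **A mixed model would rest on few groups.** Three sets of child and adolescent groups are the stated minimum, about six groups if each set holds one of each. This stands and shapes the fix.

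A possible unseen analysis plan does not remove the point, because the article itself names the model, the output and the one clustering adjustment.

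**Conclusion.** The omission is real. No stated effect model allows for Young SMILES group, although the plan delivers treatment in groups and expects correlation within them. If the group ICC is positive, the 95% intervals for the HRQoL effects are too narrow.

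At 30:30 the true standard error is about 5%, 10% and 18–19% larger than reported for ICCs of 0.05, 0.10 and 0.20 with five index children per group, with coverage of about 94%, 93% and 90–91%. With about 3.3 index children per group the excess is about 3%, 6% and 11%. At 40:20 it is smaller in every case.

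These sizes rest on the assumed ICCs, equal total variance in the two arms and, for the lower set, 1.5 attending children per family. The point concerns the effectiveness intervals and the care needed in deriving the ICC, not the feasibility findings.

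**What to change.** 1. **Main effectiveness analysis.** Replace the ordinary regression with a partially nested linear mixed model: a random intercept for Young SMILES group in the intervention arm only, control families as singletons, the same baseline and sex adjustment, and small-sample degrees of freedom (Satterthwaite or Kenward-Roger).
2. **Sensitivity analysis.** Because groups are few, also report the 95% intervals over a range of assumed group ICCs, for example 0 to 0.20, so that the conclusion does not hang on one imprecise variance component.
3. **All-children analysis.** Allow for both family and group.
4. **ICC for the definitive trial.** State that it comes from index children or from a model that includes a family effect.

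The cost is a change of analysis wording and a few lines of code. Group membership should already be known from delivery, so no new outcome data are needed. The downside is slightly wider intervals and an imprecisely estimated group variance.

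### The HRQoL model adjusts for baseline score and sex but not for age, site or allocation phase, although randomisation appears to use all three

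*Protocol article*

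**What the plan says.** **Model.** Under Intervention effectiveness the protocol article states: "we shall use standard linear regression to examine change in our HRQoL measures", "adjusting for baseline scores and the sex of the child". This is the whole adjustment set. On reporting, "The presentation of the analysis will focus on point estimates and associated 95% confidence intervals". On use of the results, "After obtaining point estimates of intervention effect and measure of variability of the outcomes, we will be able to design a definitive trial".

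**Randomisation.** The Randomisation section describes 1:1 allocation of families and names no stratifiers. Table 4 under Protocol changes lists changes made since the trial commenced, all approved. One is a move to other software, partly for "the ability to stratify by age and site, without incurring costs". Another is "Addition of 2:1 randomisation allocation procedures (2 Young SMILES intervention; 1 control) to expedite start of intervention groups". The table gives no date for either change and no count of families randomised before them.

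**Structure.** The Sample size section gives 60 families and three recruitment sites. The intervention section gives two age bands, 6–11 and 12–16. No section revises the model after the changes in Table 4.

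**The concern.** The model keeps sex, which is not named as a stratifier, and leaves out age and site, which are. Stratified randomisation balances the arms on age and site. If those factors predict the outcome, a model without them treats the balanced variation as noise. The standard error is then too large, and so is the residual SD that is to be carried into the next trial. Age is a plausible predictor here because it affects how HRQoL is measured: the youngest children use a shorter response scale on the Pediatric Quality of Life Inventory, and KIDSCREEN is completed by parent proxy below age 8.

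The change of ratio raises a different issue. Randomisation protects the comparison within each ratio. If the two phases are pooled without a phase term, the Young SMILES arm holds a larger share of late families than the control arm, and any early-late difference in outcome enters the arm contrast. That contrast and the residual SD are what the protocol intends to take forward.

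**Working it through.** **Inputs.** From the protocol article: 60 families, 1:1 at first, 2:1 added later, two age bands, three sites. Not in the document, so assumed and shown as ranges: the number m of families randomised at 1:1 before the switch, with all later families at 2:1; the early-late outcome difference D; and the share of residual variance explained by age and site.

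**The plan's own figure.** 60 families at 1:1 gives 60/2 = 30 per group, as stated. There is no power calculation to reproduce.

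**Arm composition after a switch.**

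- Late share, Young SMILES = (2/3)(60 − m) / [m/2 + (2/3)(60 − m)]
- Late share, control = (1/3)(60 − m) / [m/2 + (1/3)(60 − m)]
- Bias of the pooled contrast = (difference in late shares) × D

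For m = 30, Young SMILES has 15 + 20 = 35 families, with late share 20/35 = 57.1%. Control has 15 + 10 = 25, with late share 10/25 = 40.0%. The gap is 17.1 points.

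| m at 1:1 | Late share, Young SMILES | Late share, control | Gap (points) | Bias, D = 0.2 SD | Bias, D = 0.5 SD |
|---|---|---|---|---|---|
| 0 or 60 | – | – | 0 | 0 | 0 |
| 10 | 87.0% | 76.9% | 10.0 | 0.020 | 0.050 |
| 20 | 72.7% | 57.1% | 15.6 | 0.031 | 0.078 |
| 30 | 57.1% | 40.0% | 17.1 | 0.034 | 0.086 |
| 40 | 40.0% | 25.0% | 15.0 | 0.030 | 0.075 |
| 50 | 21.1% | 11.8% | 9.3 | 0.019 | 0.046 |

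The bias is in SD units. It is an upper figure, because adjustment for baseline score removes whatever part of D the baseline already carries.

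**Cost of a phase term, m = 30.** The standard error without it is √(1/35 + 1/25) = 0.2619 SD. With it, the information is 15×15/30 + 20×10/30 = 7.5 + 6.667 = 14.167, and the standard error is √(1/14.167) = 0.2657 SD. The ratio is 0.2657/0.2619 = 1.015, a rise of about 1.5%.

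**Leaving out the stratifiers.** A simulation used 3,000 runs of 60 families in six equal age-by-site strata, balanced 1:1 within strata, with no true effect and no other covariates.

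| Residual variance explained by strata (assumed) | Mean 95% CI width, strata omitted | Mean width, strata included | Coverage, omitted | Coverage, included |
|---|---|---|---|---|
| 0% | 1.03 SD | 1.03 SD | 94.5% | 94.3% |
| 10% | 1.03 SD | 0.98 SD | 95.4% | 94.3% |
| 20% | 1.03 SD | 0.92 SD | 97.7% | 95.6% |
| 30% | 1.03 SD | 0.86 SD | 98.3% | 95.1% |

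The spread of the estimates was the same under both models (for example 0.225 SD at 20%). So the loss lies in the stated uncertainty and not in the estimate. For the next trial, at 20% the residual variance without the strata is 1/0.8 = 1.25 times the variance with them. Sample size scales with residual variance, so a definitive trial that adjusts for these factors would be planned about 25% too large.

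The phase term and the strata were checked separately. The full model with both was not simulated.

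**The case against.** The strongest reply has four parts.

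**The switch is not described.** Table 4 does not say when 2:1 came in, whether it applied to every later family, or how many had been randomised at 1:1. Baseline interviews waited for enough same-band referrals at a site, and the first group ran only in January 2018, so the number at 1:1 could be small. This stands. At m = 5 the late shares are 36.67/39.17 = 93.6% and 18.33/20.83 = 88.0%, a gap of 5.6 points, and the gap goes to zero at either extreme. The bias must therefore be stated conditionally.

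**The stratification is inferred.** The document names a capability of the software and sets out no scheme. This also stands, although the table gives that capability as a study requirement and a reason for the change.

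**The size is small.** A bias of 0.086 SD against a standard error of 0.262 SD is about a third of one standard error, in a feasibility trial with no formal power calculation and whose main focus is recruitment and participant flow. This stands as to weight, but the estimate and the SD are still meant to feed a design.

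**Extra terms cost precision in 60 index children.** The cost is slight: about 1.5% in the standard error for phase at m = 30, and almost nothing for the strata even when they explain no variance.

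A reader might also infer that early and late families must differ because new sites joined and because "the primary outcome point was changed to 4 months, without altering the 6- and 12-month time points". The documents do not support that. The Recruitment sites section places the service-centre closures, which led to the two new sites, before recruitment began. Table 4 dates neither the follow-up change nor the ratio change, so the two are not shown to coincide. Nor does leaving out stratifiers bias the estimate when the ratio is constant.

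**Conclusion.** The point holds in a limited form. The protocol itself fixes the covariates, and the list does not follow the randomisation that its own table of changes indicates.

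Leaving out age and site costs precision. On the assumption that they explain 10 to 30% of residual variance, the 95% interval is about 1.03 SD wide instead of 0.98 to 0.86 SD, and the residual SD carried forward is too large.

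Leaving out allocation phase can bias the pooled contrast by about 0.02 to 0.09 SD before any reduction from baseline adjustment. That rests on three assumptions: families were randomised under both ratios, the switch fell after 10 to 50 of 60 families, and early and late families differ by 0.2 to 0.5 SD. The documents establish none of these, though an addition made after the trial commenced makes the first likely. The change is worth making because it is cheap and the estimates are meant for reuse; the evidence does not show that the result would be seriously distorted.

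**What to change.** Change the main HRQoL model to: outcome on arm, baseline score, sex, age band, site and, if both ratios were used, allocation phase (1:1 or 2:1). Use the same terms in the secondary analysis of all children, which keeps its robust standard errors for families. State the stratification scheme and report the number of families randomised per phase and arm, so that a reader can see where the trial falls in the table of gaps. If any of these terms is left out, say why.

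The cost is a line in the analysis text and about 4 degrees of freedom (age band 1, site 2, phase 1). With 60 index children and no attrition, the residual degrees of freedom fall from 60 − 4 = 56 to 52. All the variables are known at randomisation.

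Do not add actual time from baseline to follow-up to the main model. It is measured after randomisation and may depend on arm, since the move to 4 months was prompted by families still attending Young SMILES; at most it belongs in a sensitivity analysis. Comparing feasibility rates by arm within phase is not useful either: with a switch after 50 families, only about 10/3 ≈ 3 late control families would be expected.
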